**Discontinuation**

After recruitment, women may withdraw from the trial if they do not wish to participate.

**Registration and reporting of suspected adverse events**

Complications and the number of women requiring surgical intervention (e.g. for on-going pregnancy, retained products of conception, ectopic pregnancy) will be recorded.

Any unexpected and serious side effects and suspected adverse reactions will be immediately reported to the project leader as well as the trial steering committee. The regional ethics committee will also be notified according to local regulations.

Any unexpected adverse event that occurs during the study will be reported to Läkemedelsverket according to LVFS 2003:6 (electronically). This will also be recorded in the patient file which will be kept (with the other study documents) for at least ten years.

***Trial start date***

The trial is planned to start in September 2001 and end in September 2006.

Amended 12 Dec 2006. Due to reorganization of the clinic the trials start was postponed to start in February 2007and to end in October 2010.

***Statistical analysis; power calculations - sample size***

***Sample size***

The main outcome of the study is to detect any difference in expulsion rate between women assigned to the early and the delayed IUC insertion groups. Since no data on expulsion rates of IUC after early post medical insertion is available at the time of the study start we assumed that expulsion rate after early insertion post medical abortion is similar to the expulsion rate after immediate insertion post surgical abortion. In a previous study of immediate IUC insertion post surgical abortion, the expulsion rate during the first year was found to be 15,4 % in the immediate group compared to 2,8% in the delayed insertion group (6). With 60 patients in each randomized group we will have a power of 78% in a one-sided test (alpha-level: 5%) to detect a difference between the groups of the same magnitude as in the study by Gillett et al. To evaluate the differences between the groups regarding independent nominal data such as expulsion, side-effects and compliance, the chi squared test will be used. Continuous variables with a normal distribution, such as age will presented as medians (range) and compared using Mann-Whitney U-test. Also discrete numerical variables such as parity and bleeding patterns will be presented as medians (range) and assessed for normality and comparison using the Mann-Whitney U-test. Results will be considered statistically significant if P-value < 0·05.

The data will be analysed using the intention-to-treat principle, including all women in the groups as randomized. Numbers and proportions of women receiving IUC insertion will be calculated by intervention. Both interventions will be compared using both absolute and relative measures with 95% confidence intervals.

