**Randomization procedure**

Women who volunteer to participate in the study will be assigned, within each stratum (Cu-IUD or LNG-IUS), to either group at a ratio of 1:1 using a computer generated randomization list. The randomisation procedure is a third party concealed randomisation. A study nurse, not directly involved in the study, will perform block randomisation, 10 subjects to each block, and create opaque, numbered, envelopes containing the randomisation group for each participant. Randomisation will occur upon opening the envelope consecutively after the participant has signed informed consent to participate.

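### The 78% power belongs to a one-sided 5% test, but the analysis wording points to a two-sided test, for which 60 per arm gives about 67%

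*Protocol*

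**What the plan says.** All the relevant text except the allocation ratio is in the Protocol, section Statistical analysis; power calculations - sample size.

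- **Design basis.** "With 60 patients in each randomized group we will have a power of 78% in a one-sided test (alpha-level: 5" per cent). The effect comes from an earlier study of IUC insertion after surgical abortion, with expulsion of "15,4 % in the immediate group compared to 2,8% in the delayed insertion group (6").
- **Aim.** The main outcome is framed as "to detect any difference in expulsion rate" between the early and delayed groups.
- **Test.** For comparisons "regarding independent nominal data such as expulsion, side-effects and compliance, the chi squared test will be used".
- **Threshold.** "Results will be considered statistically significant if P-value < 0·05". No sidedness is given here.
- **Estimation.** The two interventions are to be compared on absolute and relative scales with 95% confidence intervals.

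Under Randomization procedure, women are assigned "to either group at a ratio of 1:1 using a computer generated randomization list". Expulsion at 6 months is the primary outcome.

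**The concern.** The size of the trial is justified by one kind of test and the analysis is described in terms that fit another. A chi-squared P-value in its usual form ignores direction. A 95% interval corresponds to a two-sided 5% test, whereas a one-sided 5% test corresponds to a 90% two-sided interval. The term one-sided appears only in the power sentence.

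Two things are at stake. First, if the analysis is two-sided, the chance of missing the planned 12.6-point excess is larger than the 22% that the power statement implies. Second, the primary decision rule is open. The same data could be called significant by an analyst who follows the power sentence and not significant by one who follows the rest of the paragraph, and that choice could be made after the results are known.

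**Working it through.** **Inputs.** From the sample size paragraph: n = 60 per arm, p1 = 0.154 (early), p2 = 0.028 (delayed), alpha = 0.05. Allocation is 1:1 (Randomization procedure). No dropout allowance enters the stated calculation, so none is applied here.

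**Formula (normal approximation, pooled variance under the null, no continuity correction).**

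Power = Φ[(d − z·SE0) / SE1], where

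- d = 0.154 − 0.028 = 0.126
- mean rate = (0.154 + 0.028)/2 = 0.091
- SE0 = √(2 × 0.091 × 0.909 / 60) = 0.0525
- SE1 = √[(0.154 × 0.846 + 0.028 × 0.972) / 60] = 0.0512

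**Step 1: reproduce the stated figure.** One-sided, z = 1.645: (0.126 − 1.645 × 0.0525)/0.0512 ≈ 0.773, and Φ(0.773) = 78.0%. This matches the protocol. Solved for n at 78% power, the formula returns exactly 60 per arm.

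**Step 2: same formula, two-sided.** z = 1.960: (0.126 − 1.960 × 0.0525)/0.0512 ≈ 0.451, and Φ(0.451) = 67.4%.

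**Step 3: dependence on method.** Exact values come from enumerating all outcomes with 60 per arm.

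| Method | One-sided 5% | Two-sided 5% |
|---|---|---|
| Pooled normal (reproduces the 78%) | 78.0% | 67.4% |
| Unpooled normal | 79.2% | 69.1% |
| Arcsine | 82.4% | 73.1% |
| Continuity-corrected normal | 67.3% | 55.0% |
| Exact, uncorrected chi-squared | 82.8% | 71.8% |
| Exact, Yates-corrected or Fisher | 72.1% | 57.0% |

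Every two-sided value is below 78%. By the pooled formula, 78% two-sided power would need 77 per arm, and 80% would need 81.

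**Step 4: can the decision differ on the same data?** Take, for illustration, 9/60 expulsions early and 3/60 delayed.

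- Difference = 10 points, pooled rate 0.10, z = 0.10/√(2 × 0.10 × 0.90/60) = 1.826.
- Uncorrected chi-squared: P = 0.068, not significant. Halved for a one-sided test: P = 0.034, significant.
- Interval for the difference, with SE = √[(0.15 × 0.85 + 0.05 × 0.95)/60] = 0.054: the 95% CI is −0.6 to +20.6 points and includes zero. The 90% CI is about +1.1 to +18.9 points (0.10 ± 1.645 × 0.054) and excludes it.

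So a one-sided P-value reported beside the planned 95% CI can contradict it.

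**The case against.** The strongest reply is that nothing is miscalculated or concealed: the 78% is right for the test it names, and the protocol labels it one-sided. This stands. A reader might infer an arithmetic error, but the figure reproduces, so the fault is an inconsistency between the design statement and the analysis wording.

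A second reply is that the protocol never says two-sided. The only explicit statement of sidedness is one-sided, the chi-squared and P < 0.05 sentences are generic, and a one-degree-of-freedom chi-squared test can be used directionally. A direction is also documented: Scientific background reports somewhat higher expulsion after immediate insertion, and the assumed rates run the same way. This stands in part. A reader might infer that the 78% belongs to a test the trial will certainly not run, which is firmer than the text allows. Two-sidedness is an inference, though a strong one, because the non-directional aim and the 95% intervals both favour it. The expected direction is not offered as a reason for a one-sided primary test. An analysis plan not seen here may settle the matter, but it would not remove the conflict within the protocol.

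Third, 67% is one formula's answer. This stands too: for the uncorrected chi-squared test the exact miss rate is about 28%, not one in three.

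Finally, a reader might infer that a non-significant result would be presented as proof that early insertion does not raise expulsion. The protocol sets no such claim and already commits to interval estimates.

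**Conclusion.** The point holds as an inconsistency within the protocol. The power statement rests on a one-sided 5% test, while the analysis wording points to a two-sided 5% test and specifies no one-sided primary analysis. Like for like, power falls from 78.0% to 67.4%, about 11 points, and the risk of missing the assumed difference rises from 22% to about 33%. By exact calculation the two-sided power is about 72% (uncorrected chi-squared) or about 57% (Yates or Fisher), which is 6 to 21 points below the stated 78%. The size of the gap depends on the method, but its existence does not.

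This rests on three assumptions: the primary test is two-sided, which is inferred; 60 women per arm contribute to the comparison; and the cited first-year rates are taken as the protocol uses them. The finding does not show that the 78% was computed wrongly, nor that the trial must recruit more women.

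**What to change.** State in the sample size section that the primary expulsion test is two-sided at 5%, in line with the chi-squared test and 95% intervals already planned. Restate the power for 15.4% against 2.8% with 60 per arm as about 67%, naming the pooled normal approximation. Say which version of the chi-squared test will be used and give its exact power: about 72% uncorrected, about 57% with Yates correction.

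If the sponsor does intend a one-sided primary test, the 78% can stay. The protocol must then say so before data are seen, give the reason, and bring the aim, the P-value rule and the interval (90% two-sided, or a one-sided 95% bound) into line.

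The cost is wording and, on the two-sided route, a less favourable stated power. No extra patients are needed for this correction. Keeping 78% two-sided by the same formula would take 77 per arm, which is the sponsor's choice and not a requirement of this point.

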**Allocation and treatment**

Designated study nurses and doctors will be responsible for recruiting and examining study participants at the outpatient clinic. Eligible women with a pregnancy up to 63 days gestation who elect to participate in the study and who sign an informed consent form will be randomised into either :

Group 1 (early IUC insertion on day 5-9 after mifepristone)

or

Group 2 (outpatient standard follow-up and IUC insertion at 3-4 weeks after mifepristone) .

Study participants will be administered mifepristone and misoprostol according to routine. All women will be screened for bacterial vaginosis and Chlamydia infection, and treated if positive but not excluded from participation. Women will receive mifepristone (Mifegyne®, Exelgyn, Paris, France) 200 mg orally at the clinic. The day when mifepristone is administered counts as Day one. Thirty-six to 48 hours later women self administered 800 mcg misoprostol vaginally (Four tbl Cytotec® 200 mcg, Pfizer, New York, USA).

An ultrasound examination will be performed prior to insertion of the IUC, and the anterior-posterior thickness of the endometrium recorded as well as the presence of any remaining products of conception. Women diagnosed with a continuing pregnancy or a missed miscarriage, or with any surgical intervention or untreated genital infection after the abortion treatment will excluded from the trial.

Intensity of pain will be recorded on the visual analogue scale (VAS) ranging from zero to ten (worst possible pain) directly after IUC insertion before any use of analgesia.

Serum hemoglobin (S-Hb) and serum human chorion gonadotropin (S-hCG) will be determined on treatment day one (the day of mifepristone administration), on the day of IUC insertion, and at four weeks follow up.

The patients will be scheduled to return for a follow-up visit four weeks after the IUC insertion. Any complications such as genital infection, and expulsion will be recorded.

Women will be advised to keep daily records (starting on day one) on the bleeding pattern and notes of any adverse events as well as any concomitant medication. Intensity of bleeding will be reported in relation to the individual woman's normal menstrual bleeding on a scale from sparse (much less than menstrual bleeding) to heavy (much heavier than menstrual bleeding).

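### The rule for numerical variables prescribes medians and an unadjusted, unstratified Mann-Whitney test even for normal data, and names no effect estimate with a confidence interval for them

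*Protocol*

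**What the plan says.** Under Sample size, the protocol's rule for continuous data is: "Continuous variables with a normal distribution, such as age will presented as medians (range) and compared using Mann-Whitney U-test". Parity and bleeding patterns, classed as discrete numerical variables, also get medians (range) and are to be "assessed for normality and comparison using the Mann-Whitney U-test". Nominal data are handled separately: for "independent nominal data such as expulsion, side-effects and compliance, the chi squared test will be used". The section closes with a general commitment: "Both interventions will be compared using both absolute and relative measures with 95% confidence intervals". The sentence just before it concerns proportions: "Numbers and proportions of women receiving IUC insertion will be calculated by intervention".

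Two other sections bear on the point. Randomization procedure allocates women 1:1 within strata defined by device, copper or levonorgestrel. Allocation and treatment gives the haemoglobin schedule: "Serum hemoglobin (S-Hb) and serum human chorion gonadotropin (S-hCG) will be determined on treatment day one", then "on the day of IUC insertion, and at four weeks follow up". Bleeding patterns are a declared secondary outcome. Haemoglobin is neither listed as an outcome nor mentioned in the statistical section.

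**The concern.** A rule that opens by naming normality would be expected to lead to means and a comparison of means. This one leads to the median, the range and a rank test, and the next sentence reaches the same place for discrete data. Read literally, the second sentence makes the Mann-Whitney test a check of normality, which it is not. Read charitably, normality is checked somehow and the result changes nothing.

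Three consequences follow for numerical outcomes.

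- **No estimate.** A median (range) per arm with a Mann-Whitney P-value is not a between-group difference with an interval, yet the section promises intervals without limiting them to proportions. Bleeding pattern, a declared secondary outcome, is affected.
- **No stratum.** Randomisation is stratified by device, but the stated test is not.
- **No baseline.** S-Hb is available from day one, but the only method stated for continuous data compares two groups on one value each.

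At stake are precision and interpretability of secondary comparisons in a trial of 60 women per arm, not the primary conclusion.

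**Working it through.** **1. The plan's own figure.** Inputs from Sample size: 60 per arm, expulsion 15.4% versus 2.8%, one-sided 5%. With the pooled-variance normal approximation:

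- Mean proportion = (0.154 + 0.028)/2 = 0.091.
- Null standard error = √(2 × 0.091 × 0.909/60) = 0.0525.
- Alternative standard error = √((0.154 × 0.846 + 0.028 × 0.972)/60) = 0.0512.
- Power = Φ((0.126 − 1.645 × 0.0525)/0.0512) = 78.0%.

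This reproduces the stated 78%. It rests on a binary outcome, so nothing below alters it.

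**2. Cost of the rank test itself.** For normal data the asymptotic efficiency of Mann-Whitney relative to the t-test is 3/π = 0.955, so 60 per arm act like 60 × 0.955 ≈ 57.

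**3. Gain from using day-one S-Hb.** Adjusting for a baseline value with correlation r multiplies the residual variance by 1 − r². The protocol gives no r, so a range is shown.

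| Assumed r | Remaining variance | Reduction | Equivalent sample, 1/(1 − r²) |
|---|---|---|---|
| 0.3 | 0.91 | 9% | 1.10 |
| 0.5 | 0.75 | 25% | 1.33 |
| 0.6 | 0.64 | 36% | 1.56 |
| 0.7 | 0.51 | 49% | 1.96 |

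**4. The same in power terms.** Assume a normal outcome, a true difference of 0.5 SD, 60 per arm and two-sided 5%. The protocol gives neither an SD nor a target difference for haemoglobin, so this is illustration only. Power = Φ(0.5/(s√(2/60)) − 1.96), with s = 1 for the t-test, 1/√0.955 for Mann-Whitney and √(1 − r²) for the adjusted model.

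| Analysis | Formula | Simulation (4,000 runs per setting) |
|---|---|---|
| Mann-Whitney | 76% | 75–77% |
| t-test, unadjusted | 78% | 77–78% |
| Linear model, r = 0.3 | 82% | 82% |
| Linear model, r = 0.5 | 89% | 87% |
| Linear model, r = 0.7 | 97% | 96% |

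The rank test costs about 2 points. Baseline adjustment gains more, by an amount that depends on r.

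**5. A covariate to avoid.** Time since mifepristone may look like a natural addition to the S-Hb model. Insertion is at 5–9 days in Group 1 and at 3–4 weeks (21–28 days) in Group 2, with follow-up 28 days later. Follow-up therefore falls at about days 33–37 versus 49–56, with no overlap. Assume equal spread over whole days within each window.

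- Within-arm variances are (5² − 1)/12 = 2.00 and (8² − 1)/12 = 5.25, mean 3.63.
- Arm means are 35 and 52.5, so the between-arm variance is (17.5/2)² = 76.6.
- Arm explains 76.6/80.2 ≈ 95% of the covariate's variance, and the variance of the arm effect is inflated by about 80.2/3.63 ≈ 22.

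That would swamp any gain in step 3, and it would adjust away part of what was randomised.

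**The case against.** The strongest reply is that this is one loosely worded sentence. Mann-Whitney is valid for normal data and loses little. The only continuous variable named is age, and parity is among the discrete ones; both are baseline characteristics with no treatment effect to estimate. The phrase on normality can be read with the test attached only to the comparison. Estimators and covariates are commonly left to a statistical analysis plan, which may exist but is not at hand. S-Hb is not a declared outcome, and a Mann-Whitney test on change from day one would satisfy the rule while using the baseline.

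Much of this stands, and it rules out several stronger readings.

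- A reader might infer that none of the promised intervals can be produced. The documents do not support that. The promise follows a sentence on proportions and is met for expulsion, insertion and complications by risk differences and ratios. Even for numerical outcomes, an interval can accompany the rank test; the protocol simply does not name one.
- A reader might infer that the bleeding comparison would gain the precision in step 3. It would not. Bleeding pattern comes from a diary graded against each woman's usual menstruation, whereas 1 − r² applies to S-Hb.
- A reader might infer a decision to disregard day-one haemoglobin. The protocol states no haemoglobin analysis, so adjustment is an advisable improvement and not the correction of a stated error.

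The change-score route is open but not stated, and it is weaker. With equal variances at both times, the variance of change is 2(1 − r) times that of a single value: 1.00 at r = 0.5 and 0.60 at r = 0.7, against 0.75 and 0.51 with adjustment.

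What the reply does not remove is that the protocol fixes a method, and it is unadjusted, unstratified and at odds with its own reference to normality.

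**Conclusion.** The point holds as a minor one. The rule for numerical variables contradicts its own premise, its normality assessment has no consequence, and for numerical outcomes it names no effect estimate with a 95% confidence interval and does not reflect the device strata. These follow from the text alone.

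The size is modest. The rank test costs about 4.5% efficiency if data are normal. For S-Hb only, adjustment would cut residual variance by 25–49%, equivalent to 1.33–1.96 times the sample, if the baseline correlation is 0.5–0.7; at 0.3 the cut is 9%. Those correlations are assumptions. The benefit of stratifying by device cannot be sized from the protocol. The primary outcome, the sample size and the stated 78% power do not change.

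**What to change.** Replace the two sentences on numerical variables with a rule along these lines:

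- Summarise approximately normal variables by mean (SD) and skewed or discrete ones by median (range).
- Analyse four-week S-Hb with a linear model on arm, day-one S-Hb and device stratum, reporting the mean difference with 95% confidence interval. Do not include days since mifepristone.
- Analyse bleeding pattern and other skewed or discrete outcomes with a rank test stratified by device (van Elteren), reporting a Hodges-Lehmann difference with 95% confidence interval.
- Delete the phrase that ties the assessment of normality to the Mann-Whitney test.
- State that absolute and relative measures refer to the binary outcomes and differences to the numerical ones.

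The cost is a few sentences of analysis wording. S-Hb, device type and diary data are already collected, so no extra participants, visits or measurements are needed.

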***Ethics committees and other regulatory boards***

Permission will be obtained from the regional ethics committee.

***Funding sources***

The Swedish Research Council, Karolinska Institutet and Stockholm City County.

